### 12.4 Figure 6: Power (n=850 per group) for Variations of Differences in Treatment Engagement Between SL and XR

[figure not shown]

#### 12.4.1 Power for Secondary Effectiveness Outcomes

For the secondary outcome of treatment engagement at 30 days, Figure 7 demonstrates that regardless of the proportion engaged in treatment in the SL group, our sample size will provide >90% to detect improvements for the XR group of 8% and >80% to detect improvements of 7%. For outcomes such as self-reported days of illicit opioid use, craving and satisfaction scores, the sample size will provide 90% power to detect relatively small standardized differences (Cohen's  $d=0.16$ ) between interventions.

We don't expect the proportion of participants with an overdose event within 30 days to be high. Figure 7 shows the detectable risk ratios for different proportions of participants with overdose events in the SL group. If the proportion of those with an overdose is high (15%) in the SL group, then we'll have sufficient power to detect a  $RR=0.70$ . If the proportion of those with an overdose is high (2%) in the SL group, then we'll have sufficient power to detect a  $RR=0.25$ .

**Figure 7: Detectable Risk Ratios for Overdose Outcome as a Function of Proportion of Participants with Overdose Events in the SL Group (80% Power)**

[figure not shown]

## 12.5 Sample Size Justification for Ancillary Study

The objective of this pilot study is to examine 4-h changes in opioid withdrawal signs and symptoms among patients who have a COWS score  $<8$  and receive ED-initiated XR-BUP. We will estimate the proportion of participants that: a) experience a 5 or more point increase in COWS score in 4-h following XR-BUP administration; b) transition to moderate withdrawal (COWS score of 13-24) during 4-h after XR-BUP administration; and c) experience clinician determined precipitated withdrawal within 1-h of XR-BUP administration. A sample size of 75 was determined to be sufficient to estimate these proportions with reasonable precision. Table 5 below shows the precision (actual 95% Exact Clopper Pearson confidence interval width) for different proportions. For instance, if the proportion is 0.01 (or 1%) the 95% confidence interval will have a width (i.e., difference between upper and lower 95% confidence bounds) of .066 (or ~7%). Point estimates of 5%, 10%, and 20% will have widths of 11%, 15% and 19% respectively. A sample size of 100 will decrease these widths further.

12.5.1 Table 5: Two-Sided Exact (Clopper Pearson) 95% Confidence Intervals Width for Different Proportions

| Proportion      | 0.01  | 0.05  | 0.1   | 0.15  | 0.2   | 0.25  | 0.3   |
|-----------------|-------|-------|-------|-------|-------|-------|-------|
| Actual CI Width | 0.066 | 0.113 | 0.148 | 0.173 | 0.192 | 0.206 | 0.217 |

## 12.6 Statistical Methods

### 12.6.1 General Approach

Nominal and ordinal categorical variables will be summarized using frequencies and percentages. Continuous variables will be summarized with the following descriptive statistics: N, mean, standard deviation, median, minimum, maximum, interquartile range, and range.

No imputation of missing data will be performed in the primary and secondary analyses. Diagnostic tests and sensitivity analyses will be performed. For evaluation of effectiveness, all analyses will follow the intention to treat principle including all patients in their randomized group regardless of treatment received.

### 12.6.2 Analysis of Implementation

#### 12.6.2.1 Analysis of Primary Implementation Outcome

Sites will be assessed for each item of the site initiation checklist. Sites meeting all criteria on the checklist will have achieved competence. We will estimate the proportion of sites that achieve competence. If a substantial number of sites do not achieve competence, we will examine site level factors that may be associated with not achieving competence.

#### 12.6.2.2 Analysis of Secondary Implementation Outcomes

Several secondary implementation outcomes will be assessed at the site level at multiple times (baseline, site initiation, 6- and 12-months post site-initiation). These include number of unique ED providers administering BUP, number of ED providers prescribing BUP from the ED, number of ED providers with DATA 2000 X waivers, provider fidelity to critical action checklist, number of ED visits BUP administered in past 30 days, number of ED visits with BUP prescriptions written in past 30 days. Several community level variables will also be compared during these time periods including: number of programs accepting patients into formal addiction treatment at 7 days following the ED visits, number of programs accepting patients and providing MOUD at 7 days following the ED visits, types of systems pathways (e.g., formal, informal, feedback) in place for arranging referrals for ongoing MOUD, proportion of patients engaged in formal addiction treatment at 7 days following the ED visit, proportion of patients engaged in MOUD at 7 days following the ED visit.

To compare discrete count data over different time periods, our general approach will be to use a generalized linear mixed effects model under a Negative Binomial distribution. These models will contain fixed effects for time (baseline, site initiation, 6- and 12-months post site-initiation) and

a random effect for site. For provider counts, the models will be offset for the log of the total number of ED providers. For visit counts, the models will be offset for the log of the total number of ED visits in the past 30 days. Alternative distributions (e.g., zero-inflated Poisson) will be considered if distributional assumptions are not met. Similarly, binary outcomes will be compared using a random effects logistic regression with a random effect for site and fixed effects for time.

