### **6.2 ED Characteristics**

EDs will be chosen to represent diversity in geographical locations, and types (i.e., academic/community; and rural/suburban/urban). Participating EDs will respond to a site selection call (process initiated 4/20/2019) to have the following characteristics:

- Prevalence of patients with untreated OUD so that a target of 7-8 patients enrolled into the study per month can be met. Potential sites will provide the selection committee with ICD 10 codes for the past 12 months related to overdose, opioid use disorder, and opioid-related diagnoses.
- An emergency provider capable of serving as a site PI
- An EHR that can be queried biweekly to assess opioid-related diagnoses and provision of ED-initiated BUP.
- Information Technology (IT) availability and support to EDs to incorporate their practice and research requests with accompanied letter of support
- Wireless internet access to allow data to be entered via tablets and uploaded to a secure study server
- Ability to have SL-BUP on their formulary and available to the ED
- Pharmacy ability to store and provide the investigational drug under an investigational new drug (IND) protocol (XR-BUP will be provided to the sites)
- Ability to hire staff to conduct the study
- Commitment to the use of a single IRB (Western IRB)
- Have accessible pharmacies to fill SL-BUP prescriptions
- Community opioid treatment providers and programs for referral for OAT (not just naltrexone or non-MOUD treatment)
- ED research infrastructure
- Capability of following patients in the community

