### 7.2 Secondary Aims and Hypotheses

#### 7.2.1 Implementation Aims

To compare pre, baseline and every 3-month intervals until the site completes RCT enrollment or participation in the study, on a range of implementation outcomes focused on the Reach, Adoption, and Implementation components of the RE-AIM framework. For this analysis, pre-refers to data collected from December 3, 2019 to January 1, 2020. Baseline refers to data collected 30-day period prior to IF (February 1 -29, 2020). Sites will be assessed for the following implementation items:

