| Effectiveness                    | What is the effectiveness of SL BUP vs. XR BUP?                                                                                                                                                                                                                                      | Primary and secondary RCT outcomes                                                                                                                                                                                                                                                       |
| Adoption                         | What # of unique ED prescribers are X-waivered? Administering BUP? prescribing BUP?
What are barriers and facilitators to ED-initiated SL and XR BUP?
How do they change throughout the study?                                                                                 | Monthly study team calls
Surveys of the ED medical director and PI pre- and post IF and at the end of the enrollment period.
Monthly report cards including structured questions related to barriers and facilitators.
Field notes from trainings, learning collaborative calls |
| Implementation (and Penetration) | To what extent is the critical action checklist for ED-initiated SL and XR BUP being adhered to?
How many prescribers fully adhere to the critical action checklist?
What types of EMR-based protocols are implemented?
What are referral processes for community referral? | Review of EMR
Surveys of ED leadership and/or site PI pre- and post IF and at completion of the enrollment period                                                                                                                                                                     |
| Maintenance                      | What resources are needed to maintain the intervention post-trial?
What adaptations are needed to integrate the intervention into regular practice?                                                                                                                               | Surveys of ED leadership and/or site PI post-study                                                                                                                                                                                                                                       |

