## 7.2.2 Implementation Hypotheses

### 7.2.2.1 Emergency Department

At each time point there will be a greater:

1. Number of ED visits during which buprenorphine BUP is administered, in the ED, in the prior 30 days.
2. Number of ED visits during which patients receive a prescription for BUP, in the ED, in the prior 30 days.
3. Number of ED prescribers who are DATA 2000 X-waivered.
4. Number of unique ED prescribers who administered BUP in the ED in the prior 30 days.
5. Number of unique ED prescribers who are prescribing BUP from the ED in the prior 30 days.
6. Percent adherence to the critical action checklist for ED-initiated SL-BUP in the sampling of providers in the prior 30 days.
7. Number of ED prescribers from the sampling who fully adhere to the critical action checklist in the prior 30 days.

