### 7.2.2.2 Community

At each time point there will be a greater:

1. Number of programs accepting patients into formal addiction treatment at 7 days following the ED visits
2. Number of formal systems (e.g., formal, informal, feedback) pathways in place for arranging referrals for ongoing MOUD at each time point.
3. Proportion of patients engaged in formal addiction treatment at 7 days following the ED visit at each time point
4. Proportion of patients engaged in MOUD at 7 days following the ED visit at each time point

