### **8.8.3 Critical Action Checklist Implementation/Process Outcome**

The critical action checklist is to be used for non RCT patients only throughout the course of the study. It provides documentation of best practices for ED-initiated BUP including: evidence of clinical history and physical examination consistent with OUD; hCG testing for pregnancy in women; documentation of opioid withdrawal severity (mild, moderate or severe); ED-initiated BUP provided appropriate to the degree of withdrawal or discharge instructions for unobserved induction (if not in adequate withdrawal); BUP prescription to include adequate quantities until appointment date; referral for ongoing MOUD to include time, location and date; and naloxone dispensed/prescribed. Data are acquired by performing a medical record abstraction. A sampling of 5 ED patients administered and/or prescribed buprenorphine at the site will be performed each month, that were not entered into the RCT.

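### Once a site is enrolling, the secondary counts of ED buprenorphine visits and prescribers include RCT participants, and the two engagement items have no pre-RCT value to be compared with

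*Combined protocol and SAP*

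**What the plan says.** Protocol section 7.2.1 sets the window: "To compare pre, baseline and every 3-month intervals until the site completes RCT enrollment or participation in the study". It fixes the starting point before facilitation: "Baseline refers to data collected 30-day period prior to IF", given as February 2020. Section 12.6.2.2 uses a different grid (baseline, site initiation, 6 and 12 months after initiation). It fits a negative binomial mixed model with time as a fixed effect, site as a random effect, and an offset for total ED visits or total ED providers.

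The outcomes there include "number of ED visits BUP administered in past 30 days, number of ED visits with BUP prescriptions written in past 30 days", together with the numbers of unique providers administering and prescribing. Section 7.2.2.1 expects each to be greater at each time point, for example "Number of ED visits during which buprenorphine BUP is administered, in the ED, in the prior 30 days". The RE-AIM table in 7.2.1.2 gives EMR data as the source for the visit counts.

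Section 6.2 selects sites so that "a target of 7-8 patients enrolled into the study per month can be met", and SAP section 4.2.1 assumes 7 randomised per site per month. One implementation outcome is protected from trial enrolment, in section 8.8.3: "The critical action checklist is to be used for non RCT patients only throughout the course of the study".

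For the community, section 7.2.2.2 expects a greater "Proportion of patients engaged in formal addiction treatment at 7 days following the ED visit at each time point", and likewise for MOUD. Section 12.6.2.2 places both among the variables compared over the same periods. The RE-AIM table gives the data source for Effectiveness as "Primary and secondary RCT outcomes".

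**The concern.** These hypotheses are about whether facilitation changes what an ED does as a matter of routine. Section 8.4.9 requires an ED injection for every XR-BUP participant, ED dosing for SL-BUP participants with COWS of 8 or more, and a prescription for the SL-BUP arm. A site that changed nothing in routine care but opened enrolment would therefore record more visits with buprenorphine, and possibly more clinicians giving it. The offset does not help. RCT participants are already ED visits, so the numerator rises and the denominator does not.

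At stake is a reported increase in ED-initiated buprenorphine that reflects the trial's own enrolment. Section 3.4 wants processes that persist after the research ends. XR-BUP is supplied by the study (6.2) and participants are identified by research assistants (8.4.1), so trial-driven visits need not persist.

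The engagement items have a different problem. A change from baseline is planned with no baseline measurement to change from.

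**Working it through.** The plan states no effect size or power for these comparisons, so there is no figure of its own to reproduce.

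**Inputs**
- Fastest enrolment used here: 7 per site-month (SAP 4.2.1; protocol 6.2 says 7-8).
- Slower enrolment: 2000 participants (protocol 8.1), about 24 sites (6.1) and 20 months (12.6.4) give 2000/(24 × 20) = 4.2 per site-month.
- Allocation: 1:1 (8.4.4).
- Routine buprenorphine visits per site per 30 days, *b*: not in the documents. Assumed 5, 10, 20 and 40.

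**Apparent rate ratio with routine practice unchanged**

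Ratio = (*b* + added visits)/*b*. For example, (5 + 7)/5 = 2.40 and (5 + 4.17)/5 = 1.83.

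| *b* | Every participant adds a visit (4.2 / 7 per month) | Half of them do (4.2 / 7 per month) |
|---|---|---|
| 5 | 1.83 / 2.40 | 1.42 / 1.70 |
| 10 | 1.42 / 1.70 | 1.21 / 1.35 |
| 20 | 1.21 / 1.35 | 1.10 / 1.18 |
| 40 | 1.10 / 1.18 | 1.05 / 1.09 |

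The separate outcomes sit as follows (8.4.9):
- **Administered:** between the two columns. XR-BUP participants are dosed in the ED, and SL-BUP participants only if COWS is 8 or more.
- **Prescribed:** the right-hand column at most, because XR-BUP participants do not get the SL-BUP prescription.
- **Unique providers:** not calculable. The documents do not say how many clinicians would treat RCT participants only.

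**Chance of a significant increase**

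A negative binomial simulation compared baseline with one time point during the RCT. It used 24 sites, site as fixed effects, assumed dispersion 0.1 and 0.3, an assumed SD of 0.5 for log site rate, 400 replicates and two-sided 0.05.
- 7.5 added visits (midpoint of 7-8): 100%, 98-100%, 60-89% and 32-48% of runs at *b* = 5, 10, 20 and 40.
- 3.75 added visits: 92-98%, 54-79%, 24-38% and 12-16%.
- None added: 2-5%.

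**Effect of removing RCT visits**

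With no diversion the ratio returns to 1.00. If half of 7.5 participants per month would otherwise have had routine buprenorphine, the non-RCT count falls. The ratio (*b* − 3.75)/*b* is then 0.25, 0.62, 0.81 and 0.91 at *b* = 5, 10, 20 and 40. Neither count alone is a clean measure of routine practice.

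**Engagement**

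Section 8.8.1 collects it from enrolled participants after enrolment. Section 14.4 requires signed consent from every patient who contributes to implementation or effectiveness outcomes, and it lists three consents: two for the ancillary study and one for the trial. None covers patients treated in February 2020. No pre-RCT value can be formed from what is specified.

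**The case against.** **Scope.** A reader might infer that the implementation component as a whole is compromised. The documents do not support that. The primary hypothesis (80% of sites competent, 7.1) does not use these counts. Waiver counts, accepting programs and referral pathways are not raised by enrolling patients, and checklist fidelity already excludes RCT patients. These are secondary outcomes in a Hybrid Type 1 design.

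**A pre-enrolment contrast exists.** Sites are activated only after meeting the initiation criteria, so baseline versus site initiation precedes RCT enrolment. That stands. The criterion of at least 5 patients given ED buprenorphine (7.4.2) bears on that contrast, but it is a separate matter.

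**The size can be overstated.** Seven per month is a planning rate. At that pace 2000/(24 × 7) = 11.9 months, so the 12-month point might fall after enrolment. Participants who would have received buprenorphine anyway add nothing to the visit count. For prescriptions, if 3.5 of 7 participants would have had a routine one, the SL-BUP arm's 3.5 replace them and the net change is zero. All of this stands and is why a range is given.

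**Engagement is also recorded in the ancillary study.** True (9.11.26), so it would be wrong to say that only RCT participants supply it. But those data are patient-reported, in XR-BUP recipients with COWS below 8 at 4-10 sites, and are not a site baseline.

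**Rules may be set elsewhere.** Section 12.2.1 refers to two earlier network studies for detail, and SAP section 1.0 leaves these analyses to the Lead Node. That is possible. These documents contain no such rule, and the checklist restriction shows that they state one where it was intended.

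**Conclusion.** The point holds for ED items 1, 2, 4 and 5 in 7.2.2.1, at time points during RCT enrolment, and for community items 3 and 4 in 7.2.2.2. If routine practice is unchanged and every participant adds a visit, the apparent rate ratio for visits is about 1.8-2.4, 1.4-1.7, 1.2-1.35 and 1.1-1.2 at 5, 10, 20 and 40 baseline visits per 30 days. Each separate outcome moves less. The size rests on the assumed baseline volume and on 4.2 to 7 participants per site-month. It is substantial at low-volume sites and modest at 40 or more.

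For engagement, the contrast with baseline cannot be computed from any source the plan names.

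A reader might go further and conclude that any observed increase is an artefact. The documents do not show that. They show that the planned analysis could not tell an artefact from a real change. This should be corrected before the implementation analysis is run; it does not touch the trial's primary effectiveness comparison.

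**What to change.** - **Flag RCT visits** in the biweekly EHR reports that sites already produce (7.4.2), using the enrolment records the DSC holds (8.4.3).
- **Report both counts.** In 12.6.2.2, at each time point during RCT enrolment, give visit counts and unique-provider counts with and without RCT visits. Recount providers from the flagged visits. Subtracting enrolments fails because one clinician may treat both kinds of patient.
- **State the inference rule.** Conclude that routine practice increased only if the result does not depend on RCT visits. Say that the count without them may be biased downward by diversion of eligible patients into the trial.
- **Engagement.** Remove baseline from the two hypotheses in 7.2.2.2 and 12.6.2.2, and report engagement descriptively over RCT enrolment. Note the mid-trial change to COWS of 4 or more, which brought home induction into the SL-BUP arm (8.10; SAP 2.2.3.2) and would confound a trend over time.
- **Reconcile the time points** in 7.2.1 with those in 12.6.2.2.

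The cost is protocol wording, a flag in an existing report and a little more analysis, with no new patient data. The downside is that reported increases will probably be smaller.

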##### 7.2.1.1 ED Items

1. Number of ED visits for patients with OUD during which buprenorphine BUP is administered, in the ED, in the prior 30 days.
2. Number of ED visits for patients with OUD during which patients receive a prescription for buprenorphine BUP, in the ED, in the prior 30 days.
3. Number of unique ED prescribers who are DATA 2000 X-waivered since the last query.
4. Number of unique ED prescribers who are administering dispensing BUP in the ED in the prior 30 days.
5. Number of unique ED prescribers who are prescribing BUP from the ED in the prior 30 days.
6. What are barriers and facilitators to ED-initiated SL-BUP and XR-BUP?
7. How do the barriers facilitators change throughout the study?
8. To what extent is the critical action checklist for ED-initiated SL-BUP and XR-BUP being adhered to in the prior 30 days?
9. Number of ED prescribers who fully adhere to the critical action checklist in the prior 30 days.
10. What types of EMR-based protocols are implemented?
11. What processes for community referral for ongoing MOUD are being used?
12. What resources are needed to maintain the ED BUP post-trial?
13. What adaptations are needed to integrate the ED BUP into regular practice?

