#### 7.4.2 Implementation Criteria for Site Initiation for the Effectiveness RCT Component

1. A core group of ED physicians and APPs (2-10) trained to competence in administering SL and XR BUP formulations depending on the size and type of ED.
2. ED protocol developed for SL BUP and XR-BUP administration and referral.
3. Pharmacy procedures in place to obtain both formulations of BUP when needed (e.g., during hours of enrollment).
4. Research Associates (RAs) are hired and all training required by Lead Team and Emmes is completed to initiate trial.
5. Bi-weekly reports generated from EHR are developed and submitted to DSC including number of patients administered BUP in the ED and prescribed BUP from the ED, type of provider to include MD/DO or APP; and number of unique providers. Monthly reports to include the ICD 10 codes for opioid related diagnoses.
6. Clinically, the site provides ED-initiated BUP to at least 5 patients who would potentially meet study eligibility criteria.
7. Adherence to Critical Actions confirmed. Each individual provider who administered/prescribed buprenorphine will have at least one medical record review. A sampling of 5-10 charts of patients who are prescribed buprenorphine will be reviewed monthly. Every new prescriber will have at least one CAC completed to allow monitoring and feedback

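### The count of fully adherent prescribers comes from a chart sample, but the only offset given for provider counts is all ED providers, so the modelled rate mixes adherence with how many prescribers were reviewed

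*Combined protocol and SAP*

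**What the plan says.** The outcome appears in three places in the protocol, in three forms:

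- Section 7.2.1.1, item 9, has a head count with no mention of sampling: "Number of ED prescribers who fully adhere to the critical action checklist in the prior 30 days".
- Section 7.2.2.1, hypothesis 7, expects a rise in that count at each time point but limits it to the sample: "Number of ED prescribers from the sampling who fully adhere to the critical action checklist in the prior 30 days". Hypothesis 6 is the percent companion: "Percent adherence to the critical action checklist for ED-initiated SL-BUP in the sampling of providers in the prior 30 days".
- Section 12.6.2.2 lists only "provider fidelity to critical action checklist", without saying whether that means the count or the percent.

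On method, section 12.6.2.2 says "our general approach will be to use a generalized linear mixed effects model under a Negative Binomial distribution", with fixed effects for time and a random effect for site. The offset rule is "For provider counts, the models will be offset for the log of the total number of ED providers". No separate denominator is given for outcomes seen only in a sample. Binary outcomes get a random-effects logistic model.

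The review sample is also described in more than one way. Section 7.4.2 says "A sampling of 5-10 charts of patients who are prescribed buprenorphine will be reviewed monthly", and adds at least one record review for each clinician who gave buprenorphine and one checklist for every new prescriber. Section 8.8.3 says "A sampling of 5 ED patients administered and/or prescribed buprenorphine at the site will be performed each month", restricted to patients outside the RCT.

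The SAP does not fill the gap. Its introduction assigns all site-implementation analyses to the Lead Node and does not specify them, so section 12.6.2.2 is the only specification.

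**The concern.** An offset should measure the population in which the event could have been observed. For counts taken from the whole electronic record (clinicians administering, prescribing or holding a waiver), all ED providers is a sensible exposure. Full checklist adherence, however, can be seen only in prescribers whose charts were reviewed. Providers who were not reviewed, or who gave no buprenorphine in the window, add to the denominator but cannot add to the numerator.

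What is at stake is the direction of change. The number reviewed has reasons to move between time points. The chart sample is 5-10 a month in the site-initiation criteria and 5 a month in section 8.8.3. New prescribers trigger extra checklists. Hypotheses 4 and 5 in section 7.2.2.1 themselves predict more active prescribers, and more active prescribers means more distinct people in the same number of charts. A rise in the modelled rate could then be read as better fidelity when fidelity has not changed, and a fall could hide a real improvement.

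**Working it through.** The plan states no rate, power or precision for this outcome, so there is no figure to reproduce. The check is how the modelled rate behaves.

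**Inputs from the protocol.** Offset: log of all ED providers (12.6.2.2). Charts per month, c: 5 (8.8.3) or 5-10 (7.4.2).

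**Assumed, because the protocol does not give them.** T, total ED providers: 60. K, equally active buprenorphine prescribers: 2 to 40. a, the true proportion of prescribers who fully adhere: 0.60 unless stated. Adherence is treated as a property of the prescriber, so several charts for one person do not change that person's class.

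**Formulas.** Expected distinct prescribers among c charts: D = K × (1 − (1 − 1/K)^c). Modelled rate under the planned offset: a × D / T. Rate with reviewed prescribers as denominator: a × D / D = a.

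**Step 1: adherence constant, charts go from 5 to 10, same T.** The rate ratio is D(10)/D(5).

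| K | D, 5 charts | D, 10 charts | Rate ratio |
|---|---|---|---|
| 2 | 1.94 | 2.00 | 1.03 |
| 5 | 3.36 | 4.46 | 1.33 |
| 10 | 4.10 | 6.51 | 1.59 |
| 20 | 4.52 | 8.03 | 1.77 |
| 40 | 4.76 | 8.95 | 1.88 |

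If every chart belongs to a different prescriber, the ratio is 10/5 = 2.0. The effect is small where only a few clinicians prescribe and large where ten or more do. With T = 60 and a = 0.60 throughout, the modelled rate runs from 0.60 × 1.94/60 = 0.019 to 0.60 × 8.95/60 = 0.090.

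**Step 2: adherence constant, 5 charts, uptake grows from 2 to 20 active prescribers.** The ratio is 4.52/1.94, about 2.3: an apparent improvement with none present.

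**Step 3: adherence rises from 0.60 to 0.80 while charts fall from 10 to 5, K = 20.** The ratio is (0.80 × 4.52)/(0.60 × 8.03) = 3.62/4.82 = 0.75. The direction is wrong.

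**Step 4: c, K and T all fixed, adherence rises from 0.60 to 0.80.** The ratio is 0.80/0.60 = 1.33. Here the planned model gives the right answer.

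**Step 5: every active prescriber is reviewed, so D = K.** With a = 0.60 and T = 60, the rate is 0.60 × 5/60 = 0.05 at K = 5 and 0.60 × 40/60 = 0.40 at K = 40. Complete review removes the sampling effect but leaves uptake mixed with adherence.

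With reviewed prescribers as the denominator, the rate is 0.60 in Steps 1, 2 and 5, and the ratio is 0.80/0.60 = 1.33 in Steps 3 and 4.

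**The case against.** The strongest reply is that section 12.6.2.2 never says the offset applies to this outcome. It names its provider head counts as numbers, lists the checklist item separately as fidelity, and calls the model a general approach. If the percent in hypothesis 6 is what will be analysed, the offset is irrelevant. This stands in part: applying the offset here is an inference. It is the natural one, because hypothesis 7 is a count of providers and only one rule for provider counts exists. The ambiguity itself needs settling.

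Second, adherent prescribers over all ED providers might be intended. The RE-AIM table in section 7.2.1.2 puts the question of how many prescribers adhere under implementation and penetration. But penetration needs a numerator drawn from the whole department; a sampled numerator over an unsampled roster does not measure it.

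Third, the change might seem to duplicate hypothesis 6. There is overlap, but percent adherence to a checklist and the share of prescribers who meet all of it are different quantities, and hypothesis 6 is limited to SL-BUP.

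Fourth, the hypotheses concern change, not level, and a stable ratio of reviewed to total providers largely cancels from the time contrast, as Step 4 shows. This stands, and it limits the problem to periods when that ratio moves.

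A reader might infer that the count can only come from the 5-10 monthly charts. Section 7.4.2 does not support that, because it adds a review of each buprenorphine provider and each new prescriber. Fixed ceilings such as 5 over the roster therefore do not follow from the text. Those added reviews are not said to recur every 30 days, so they soften the problem without removing it.

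**Conclusion.** The point holds as a mismatch between numerator and denominator in one secondary implementation outcome. On the natural reading, the modelled rate is adherence × (distinct prescribers reviewed / all ED providers). At constant adherence, a change from 5 to 10 charts multiplies it by about 1.6 to 2.0 when 10 to 40 prescribers are active (1.03 to 1.33 with 2 to 5). A true rise from 60% to 80% can appear as a ratio of 0.75 if charts halve with 20 active prescribers. These figures rest on the assumed prescriber numbers, equal activity among prescribers and an unchanged roster between the time points compared.

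A reader might go further and say that the rate tracks sample size instead of adherence. The documents do not support that: the rate reflects both, and with the number reviewed and the roster fixed it tracks adherence correctly. The proportion of sites reaching competence and the primary RCT analysis are not touched.

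**What to change.** In section 12.6.2.2:

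1. State which checklist measure is analysed: the percent, the count of fully adherent prescribers, or both.
2. For the count, use distinct prescribers reviewed in the 30-day window as the denominator. Either model adherent out of reviewed as binomial, with the random-effects logistic model already in that section, or keep the negative binomial model with log(prescribers reviewed) as the offset. Say how a prescriber with several reviewed charts is classed.
3. Keep the total-provider offset for the administering, prescribing and waiver counts.
4. Reconcile sections 7.2.1.1, 7.2.2.1, 7.4.2 and 8.8.3 on whether the count is sampled, how many charts are reviewed each month, and whether the per-provider reviews recur and count towards the outcome.

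The cost is a sentence or two of text. Intervals will be wider, because a handful of reviewed prescribers per site and window is all the data there are. It must also be confirmed that the checklist form records the prescriber: the per-provider reviews in section 7.4.2 imply it, but the content listed in section 8.8.3 does not show it.
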